## Abstract

**Background:**

Ageing populations may demand more blood transfusions, but the blood supply could be limited by difficulties in attracting and retaining a decreasing pool of younger donors. One approach to increase blood supply is to collect blood more frequently from existing donors. If more donations could be safely collected in this manner at marginal cost, then it would be of considerable benefit to blood services. National Health Service (NHS) Blood and Transplant in England currently allows men to donate up to every 12 weeks and women to donate up to every 16 weeks. In contrast, some other European countries allow donations as frequently as every 8 weeks for men and every 10 weeks for women. The primary aim of the INTERVAL trial is to determine whether donation intervals can be safely and acceptably decreased to optimise blood supply whilst maintaining the health of donors.

**Methods/Design:**

INTERVAL is a randomised trial of whole blood donors enrolled from all 25 static centres of NHS Blood and Transplant. Recruitment of about 50,000 male and female donors started in June 2012 and was completed in June 2014. Men have been randomly assigned to standard 12-week versus 10-week versus 8-week inter-donation intervals, while women have been assigned to standard 16-week versus 14-week versus 12-week inter-donation intervals. Sex-specific comparisons will be made by intention-to-treat analysis of outcomes assessed after two years of intervention. The primary outcome is the number of blood donations made. A key secondary outcome is donor quality of life, assessed using the Short Form Health Survey. Additional secondary endpoints include the number of ‘deferrals’ due to low haemoglobin (and other factors), iron status, cognitive function, physical activity, and donor attitudes. A comprehensive health economic analysis will be undertaken.

**Discussion:**

The INTERVAL trial should yield novel information about the effect of inter-donation intervals on blood supply, acceptability, and donors’ physical and mental well-being. The study will generate scientific evidence to help formulate blood collection policies in England and elsewhere.

**Trial registration:**

Current Controlled Trials ISRCTN24760606, 25 January 2012.

## Background

In the long-term, ageing populations may demand more blood transfusions, but the blood supply could be limited by difficulties in attracting and retaining a proportionately smaller and decreasing pool of younger donors. [1, 2]. One approach to increase the blood supply, especially for groups for whom supply tends to be more limited (for example, people who have O negative and B negative blood types), is to collect blood more frequently from existing donors. If more donations could be safely collected in this manner at marginal cost, then it would be of considerable benefit to blood services.

The principal risk of more frequent donation is, however, iron deficiency and a fall in haemoglobin levels [3]. Each blood donation removes about 250 mg of iron from the body. There is considerable individual variation in iron stores, dietary intake, and efficiency of absorption. If iron is not fully replaced, then donors’ iron stores become progressively depleted, leading to iron deficiency or the development of frank iron-deficiency anaemia. Iron deficiency or anaemia may result in adverse health consequences for donors and their temporary rejection from giving further donations or ‘deferral’, due to failure to meet the haemoglobin threshold required for donation. This threshold, together with limits for donation intervals, has been set to minimise iron deficiency in repeat blood donors [4].

In the absence of data from reliable randomised trials to inform policies on inter-donation intervals, the Council of Europe has provided directives for blood collection that have been open to different national interpretations [5] (Table 1). NHS Blood and Transplant (NHSBT), the sole blood provider to the National Health Service (NHS) in England, currently allows men to donate up to once every 12 weeks and women to donate up to once every 16 weeks. In contrast, some other European countries allow donations as frequently as every 8 weeks for men and every 10 weeks for women.

**Table 1 Tab1:** **Whole blood inter-donation intervals across European blood services (weeks)**

	Men	Women
**England**	12	16
**Austria**	8	10
**Finland**	8	12
**France**	8	12
**Germany**	8	12
**Ireland**	10	10
**Estonia**	10	12
**Netherlands**	10	16
**Denmark**	12	12
**Flanders**	12	12
**Wales**	12	16
**Slovenia**	12	16
**Spain**	12	16
**Scotland**	16	16

As part of their duty of care, blood services screen donors at each visit for haemoglobin levels. Across Europe, minimum thresholds of 13.5 g/dL for men and 12.5 g/dL for women must be met for donation eligibility [6]. In Canada and in the USA, the thresholds are 12.5 g/dL for both men and women [5, 7]. In England, about 3% of donors overall are not eligible to donate because of failure to meet the haemoglobin threshold at screening (unpublished data, NHSBT). Such deferral may demotivate individuals to donate in the future and directly or indirectly increase the cost of collecting blood [8, 9]. Furthermore, some donors may not attend scheduled donation appointments or may self-defer owing to symptoms, which could be due, at least in part, to iron deficiency or anaemia. Therefore, the challenge faced by blood services is to decrease the incidence of deferrals for low haemoglobin whilst increasing blood supplies to meet projections of increasing demand.

We have designed the INTERVAL trial, which is a parallel group, pragmatic randomised trial. INTERVAL has enrolled about 50,000 male and female donors at the 25 static donor centres of NHSBT located throughout England. The trial’s key anticipated contribution will be to determine optimum inter-donation intervals that maximise blood supply and maintain well-being of donors. A subsidiary aim of the INTERVAL trial is to explore suggestions that donation intervals could be tailored to donors’ capacity to donate blood safely. For example, it may be that some donors have a decreased capacity for frequent donation (for example, very lean people and/or women of childbearing age who may be predisposed to anaemia), whereas other donors may be able to donate more frequently (for example, men, heavier donors, those who carry genes predisposing to them to higher iron stores) [10–12].

We confirm that recruitment into the trial was ongoing at the time this manuscript was submitted for publication.

## Methods/Design

### Pilot work preceding this trial

Prior to the initiation of INTERVAL, we conducted the Cambridge CardioResource study [13], a study of 2,500 blood donors from the East Anglia region of the UK in order to demonstrate the feasibility of embedding research protocols within NHSBT’s routine service setting. This study showed that it is possible to recruit and consent donors and collect research samples at NHSBT donation sessions, with 99% of samples being successfully retrieved. It also demonstrated that donors could complete additional research protocols remotely by the internet [14]. The findings of this pilot study have informed the design of INTERVAL.

### Objectives

The dual objectives of INTERVAL are (1) to determine the optimum intervals between donations for men and women that maximise blood supply, maintain well-being of donors, and avoid unacceptably increasing risk of iron deficiency/anaemia and its potential complications, and (2) to explore tailoring of blood donation intervals to donors by their demographic, haematological, genetic and/or lifestyle characteristics.

### Hypothesis

We will test the hypothesis that more frequent blood donation than is currently customary in England will increase the total number of blood units collected over 2 years without adversely affecting the health or well-being of blood donors.

### Design

INTERVAL is an open, randomised, multisite trial involving the recruitment of about 50,000 male and female donors from all 25 static donor centres of NHSBT throughout England. Men have been randomly assigned to standard 12-week versus 10-week versus 8-week inter-donation intervals; and women to standard 16-week versus 14-week versus 12-week intervals (Figure 1). To explore the potential value of tailoring donation intervals to possibly relevant subgroups, we have pre-specified analysis of (a) men and women, (b) carriers of informative variants in the human haemochromatosis (HFE) gene, (c) pre- and post-menopausal women, (d) people with body mass index (BMI) <22, (e) new blood donors, and (f) subgroups based on baseline measures of iron status (for example, serum ferritin).

**Figure 1 Fig1:**
[figure not shown]
**Overall design for the INTERVAL trial.**

### Setting and participants

NHSBT collects whole blood from donors attending either static donor centres or temporary ‘mobile’ donation sessions set up at community venues such as village halls. Recruitment in INTERVAL has been restricted to donors attending the static donor centres (which are open daily during the working week), principally because ‘mobile’ sessions do not typically visit locations often enough to accommodate donors who would be allocated to the more frequent intervals being evaluated in INTERVAL. The static donor centres of NHSBT are located in Birmingham, Bradford, Brentwood, Bristol, Cambridge, Edgware, Gloucester, Lancaster, Leeds (2 sites) Leicester, Liverpool, Luton, Manchester (2 sites), Newcastle, Nottingham, Oxford, Plymouth, Poole, Sheffield, Southampton, Stoke on Trent, Tooting (South London), and West End London. To facilitate the provision of adequate training support during each site’s first week of participant recruitment, we commenced recruitment in one new centre per week. At each centre, designated trained members of staff adopted the roles of clinical and/or operational experts to supervise the work of the trial.

The overall approach used in INTERVAL has been to embed research activity within the existing operational framework of NHSBT. To support additional functions required in the trial, we have established an academic trial coordinating centre at the Department of Public Health and Primary Care, University of Cambridge. In addition to supporting the trial’s core scientific activities, the coordinating centre provides a helpdesk to respond to queries from participants about the trial, and maintains a study website [15]. The academic coordinating centre has worked closely with the INTERVAL study administration team (ISAT) based within NHSBT. For example, ISAT has supported the trial to enable participants to make appointments to give blood at intervals that are more frequent than current NHSBT practice (which is not possible through NHSBT’s routine appointment system). To enhance adherence of trial participants to their allocated donation intervals, ISAT has used more intensive and systematic efforts than used in routine NHSBT practice to remind participants about their blood donation appointments, including a systematic three-step telephone and email reminder process.

### Participant recruitment

Postal invitations to take part in the trial, which included a copy of the trial information leaflet, have been sent by NHSBT alongside routine invitations to give blood. During the first 6 months of the trial (June 2012 to January 2013), invitations were sent only to those donors who were registered at a static donor centre (approximately 147,000 invitations in total). Between January and October 2013, three additional recruitment strategies were implemented, which included invitations to groups of ‘mobile’ session donors who might be willing to attend a static centre in order to join the trial. These invitations were to donors who (1) had previously indicated a willingness to give platelets at a static centre (approximately 23,000 invitations), (2) gave blood at a ‘mobile’ session within 10 miles of a static centre (approximately 200,000 invitations), and (3) lived within 30 miles (but typically within 20 miles) of a static centre (approximately 189,000 invitations).

Donors received invitations to join the trial at their next scheduled appointment. At that visit, they were asked by the donor centre reception staff whether they had received an invitation for the trial and if they wanted to join. Donors who had not yet received or read any information about the trial but who wanted to join were given the opportunity to read the information leaflet in the waiting area before donating. If there was insufficient time to do this, or the donor wanted more time to think about joining, then a trial information pack was given to the donor to read and consider before their next donation. Donors who had read the information and were willing to take part were asked to confirm their email and telephone contact details.

### Inclusion and exclusion criteria

Participants eligible to take part in the trial are aged 18 years or older, fulfil all normal criteria for blood donation [16], and are willing to be randomised to any of the trial’s intervention groups. In addition, they must be willing to donate at one of the static NHSBT donation centres for the duration of the trial. Study-specific criteria for exclusion from the trial are lack of internet access and/or unwillingness to provide an email address for trial correspondence, since the trial mainly collects data via remote and web-based methods.

### Donor screening and obtaining informed consent

At the donor centres, donors underwent routine screening for donation eligibility, including haemoglobin measurement via a copper sulphate test, followed by a Hemocue™ test for those who failed the copper sulphate test. If the donor was not eligible to make a donation on that day, for any reason, then he/she could not join the trial on that occasion. Donors who were eligible to take part in the trial were asked if they had any further questions, which were answered either directly (aided by ‘frequently asked questions’ material provided by the research team) or forwarded to the trial ‘champion’ at the donor centre or to the trial helpline. At this point, donors were asked to complete and sign both copies of the consent form, which were checked for completion of all relevant sections and for the donor’s signature on both copies. On the ‘trial copy’ of the consent form, the carer affirmed by signature that he/she had witnessed its completion and retained this copy while providing the ‘donor copy’ to the participant. For donors who were not subsequently eligible or willing to take part, consent forms were crossed through and then destroyed.

### Randomisation, concealment of allocation, and blinding

Randomisation to three sex-specific intervention groups in the ratio 1:1:1 was undertaken at the academic trial coordinating centre using individual-level randomisation achieved by means of a computer programme built into the trial database. This programme includes a minimisation algorithm to ensure that key prognostic characteristics are balanced across the trial arms at baseline (for example, new/repeat donor status, weight and age, as shown in Table 2). Randomisation was stratified by donation centre and gender. By the nature of the trial, participants have not been blinded to the intervention group to which they have been allocated.

**Table 2 Tab2:** **Categories for minimisation variables**

	Men		Women	
**Age**	<50 years	≥50 years	<50 years	≥50 years
**Weight**	<70 kg	≥70 kg	<60 kg	≥60 kg
**Donor status**	New	Repeat	New	Repeat

### Baseline data collection

On the day following enrolment into the study, NHSBT confidentially retrieved data on participants from donor records, including donor number, donation number, donation date, email and mobile contact details, sex, month and year of birth, NHS number and previous donation and deferral history in the past 5 years. Using secure systems, these data were transferred to the academic coordinating centre to facilitate contact of participants, implementation of trial protocols, tracking of participants’ appointments and attendances throughout the trial. A few days after joining the trial, participants received two emails: one containing a uniform resource locator (URL) link and requesting completion of the trial’s baseline questionnaire, and another containing a password to access the online questionnaire. Participants’ trial IDs were embedded within the URL link using a custom tag to anonymously track completion of the questionnaire. Participants were requested to complete the questionnaire within 7 days and received two email reminders and a phone call between days 7 and 14 if they did not respond. The baseline questionnaire has been designed to take approximately 15 minutes to complete and includes the following:Compulsory questions including month and year of birth, sex, height, and weight. This information was used to verify that the questionnaire had been completed by the individual to whom it was sent, and also for minimisation algorithm described above.Quality of life questions, using the Short Form Health Survey (SF-36v2) questionnaire. The SF-36v2 is a generic measure of health status that has been reported to differentiate well between health benefits produced by a range of treatments irrespective of age, disease condition, or treatment group [17–20]. It is composed of 36 questions and produces an eight-scale profile of functional health and well-being, as well as two psychometrically-based summary measures (that is a physical component score (PCS) and mental component score) and a preference-based health utility index.Previous history of iron deficiency, which may relate to susceptibility to iron deficiency.Brief lifestyle information including, diet (particularly related to iron intake and absorption), alcohol intake, smoking and physical activity.

Only participants who returned the baseline questionnaire were eligible for randomisation. After randomisation, participants were advised of their new inter-donation interval by email and were also informed that appointments should be made through NHSBT’s ISAT team. The ISAT team was responsible for making this first appointment to coincide with the participant’s allocated donation frequency. For subsequent appointments during the trial, donors are given the option, and are encouraged, to make all appointments at their selected donor centre on the occasion of future donation visits.

Once randomised, donors’ participation in the trial was flagged on their donor record together with their allocated donation frequency. This flag is critical to (1) NHSBT donor centre staff, since it is essential for the booking of future appointments at the correct interval; (2) the academic coordinating centre’s helpdesk and the ISAT team, since the flag helps to identify donors’ status on the trial and resolve any queries; and (3) data management processes, such as retrieving data on donors at regular time-points from NHSBT’s donor database and securely transferring this information to the trial coordinating centre for the purposes of monitoring appointment bookings and attendance, deferrals, adverse events of donation, positive microbiology results and deaths.

### Blood sample collection, processing, and analysis

At the baseline donation visit at which the participant’s eligibility was assessed and consent obtained, a research sample was taken from the satellite pouch that forms part of the routine blood collection unit (that is, a separate venipuncture is not required). The research sample was collected in three tubes: 3 ml EDTA, 6 ml EDTA and 6 ml serum, which were each inverted three times before placing in rigid boxes for transport to the three NHSBT sample holding sites at Manchester, Colindale (London) and Bristol. Samples were couriered from the holding sites to the central study laboratory (UK Biocentre, Stockport, UK) for processing in the morning following collection. The large majority of samples (97%) were processed within 24 hours. Samples were kept at ambient temperature from the point of collection until completion of processing. Fluctuations in temperature were monitored at various sites and time points during the collection period.

A full blood count was performed from the 3-ml EDTA blood sample using a Sysmex XN-2000 haematology analyser (Sysmex UK Limited, Milton Keynes, UK) to generate an extended profile of blood cell indices. Full blood count results of all participants were reviewed by the Haematology Review Group to identify clinically significant results for further consideration. Following centrifugation, the 6-ml EDTA sample was used to extract two 0.8-ml plasma aliquots and buffy coat, while the 6-ml serum sample yields two 0.8-ml aliquots. The plasma, serum and buffy coat aliquots are stored at -80°C prior to planned use (such as for serum ferritin analyses and DNA extraction from buffy coat). This sample collection protocol is being repeated in all participants at their last donation prior to completing their 2-year involvement in the trial. If donors are deferred or medically withdrawn from blood donation at the time their final research sample is due, they are being offered an appointment to give a research sample.

### Data collection between randomisation and the 2-year assessment

Participants are requested via email to complete an online questionnaire every 6 months during the trial follow-up period. The follow-up questionnaires collect information on the following:Compulsory questions including month and year of birth to validate completion of the questionnaire by the individual to whom it is sent.Quality of life using the SF-12v2. This abbreviated version of the SF-36v2 was chosen to reduce time burden on participants [21], as it takes only 5 minutes to complete. We are using information from this questionnaire to monitor participants’ self-rated health during the trial and provide a means to assess potential bias of trial outcomes due to selective attrition.(Serious) adverse events ((S)AEs), which are assessed to monitor donor safety throughout their 2-year participation in the trial. Questions on (S)AEs are designed to take about 5 minutes to complete and include adverse events diagnosed/treated at hospital or by a doctor, diagnoses of low iron and symptoms associated iron deficiency (see Table 3).

**Table 3 Tab3:** **(Serious) adverse events collected at 6-month intervals after randomisation, including serious adverse events, diagnoses and symptoms of low iron**

Type of adverse event	Description
**Data collected at 6, 12, 18 and 24 months**	
Serious adverse events, diagnosed/ treated at hospital or by a doctor	Heart problems including heart attack, stroke, mini-stroke, angina, heart failure
	Falls
	Transport accidents (when in charge of a vehicle)
	New illness
Diagnoses of low iron	Diagnosis of low haemoglobin by NHSBT
	Diagnosis of anaemia by general practitioner (GP) or hospital
	Prescription of iron supplements
Symptoms	Tiredness
	Dizziness
	Feeling faint
	Fainting
	Fit or seizure
	Breathlessness
	Palpitations
	Chest pain
	Restless legs [22]
***Additional data collected at 24 months***	
Symptoms	Severity of breathlessness [23]
	Severity of palpitations (that is, resulted in ECG?)
	Severity of chest pain (that is, resulted in ECG?)
	Headaches
	Sleep disturbances
	Irritability
	Reduced ability to concentrate
	Restlessness/inability to relax
	Pica

### Data collection at the 2-year assessment

On the anniversary of participants’ 2-year involvement in the trial, an email request is sent to participants requesting completion of a final 35-minute questionnaire which collects information on the following:Month and year of birth as well as sex in order to validate the identity of the person completing the questionnaire.Quality of life using the SF-36v2 questionnaire.(Serious) adverse events. At this time-point an enhanced set of questions ask about a broader range of symptoms and the severity of selected symptoms (see Table 3).Medication and supplement use, including glucose-lowering, antihypertensive, and lipid-lowering drugs as well as use of over-the-counter dietary or vitamin supplements (with a specific additional question on whether these supplements contain iron).Cognitive function tests, including Stroop Test (attention and reaction times), Trail Making Test (executive function), Pairs Test (Episodic Memory), and Reasoning Tests (intelligence). These tests, which have been adapted from the Cardiff Cognitive Battery, have been specifically designed for cognitive testing in epidemiological settings [24]. The tests are preceded by a five-item mood questionnaire to adjust for effects that may skew results of cognitive function [25, 26].Donor beliefs and ideas about blood donation, and in particular whether increased frequency of donation raises specific difficulties or concerns; these questionnaire data will be augmented by a small number of in-depth interviews.Invitation to take part in physical activity monitoring.Recent physical activity questionnaire (RPAQ) which includes questions about physical activity during the past 4 weeks across four domains (leisure time, occupation, commuting and domestic life) [27, 28].

The administration and reminder procedures for the baseline, interim, and final questionnaires have been identical.

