#### Other secondary outcomes

Other secondary outcomes, also to be assessed at 2 years, will include the following:i)The number of ‘deferrals’ of donors over the 2 years of the trial due to low haemoglobin levels and/or other factors (for example, clinical reasons, tattoos, piercings, and foreign travel).ii)Measures of iron status, including serum ferritin and reticulocyte haemoglobin.iii)Cognitive function tests of attention, executive function, intelligence, and episodic memory.iv)Physical activity measured by accelerometry.v)Cost effectiveness.vi)Donor attitudes assessed through questionnaire responses and interviews.

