### Data analysis

#### Principles

Intention-to-treat analyses will be used, comparing groups as randomised. Results for men and women will be analysed separately. The principal pair-wise comparisons of groups for men will be between 10-wk and 12-wk, and between 8-wk and 12-wk intervals. For women, these comparisons will be between 14-wk and 16-wk, and between 12-wk and 16-wk intervals. For outcomes assessed at both baseline and at the 2-year follow-up, analyses of the 2-year follow-up measures will be adjusted for the baseline measures. Other baseline characteristics (age, centre, BMI and weight, SF-36v2 physical and mental component scores, haemoglobin and ferritin) will be adjusted for in secondary analyses. Tests of interaction will assess whether results differ between the subgroups pre-specified above. Multiple testing will be taken into account when interpreting these results. The trial will be reported according to CONSORT guidelines.

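### A mood score taken at 2 years is said to be there to adjust the cognitive results, which does not fit the baseline-only, intention-to-treat analysis and could distort the comparison

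*Protocol article*

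**What the plan says.** Cognition is one of the other secondary outcomes, assessed at 2 years: "Cognitive function tests of attention, executive function, intelligence, and episodic memory" (Other secondary outcomes).

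The tests and the mood items both belong to the final questionnaire: "On the anniversary of participants’ 2-year involvement in the trial, an email request is sent to participants requesting completion of a final 35-minute questionnaire" (Data collection at the 2-year assessment). The same section gives the purpose of the mood items: "The tests are preceded by a five-item mood questionnaire to adjust for effects that may skew results of cognitive function". The Baseline data collection section lists neither a mood questionnaire nor cognitive tests. It does list the SF-36v2, which yields a mental component score.

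Table 3 is titled as "including serious adverse events, diagnoses and symptoms of low iron". Its items include tiredness at every 6-monthly questionnaire and, added at 24 months, "Irritability", "Restlessness/inability to relax" and "Reduced ability to concentrate". The Randomisation section states that participants are not blinded.

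Under Data analysis, Principles, comparisons are by intention to treat. The rule on covariates is: "For outcomes assessed at both baseline and at the 2-year follow-up, analyses of the 2-year follow-up measures will be adjusted for the baseline measures". Other named baseline characteristics, among them the SF-36v2 mental component score, enter secondary analyses. The End-of-trial analyses section says the other secondary outcomes are handled in the same way as the physical component score. Neither section mentions mood at 2 years.

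**The concern.** A randomised comparison keeps its interpretation when the covariates are fixed before allocation. A covariate measured after up to two years on the allocated interval carries no such guarantee. If the interval changes mood, and mood is related to test performance, then conditioning on mood no longer estimates the total effect of allocation on cognition. If some unmeasured factor affects both mood and cognition, conditioning on mood also brings that factor into the comparison between arms.

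The article itself makes an effect on mood plausible. Mood-like complaints are collected as symptoms linked to low iron, iron deficiency is named as the principal risk of donating more often, the Discussion expects to learn about mental well-being, and the trial is open.

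What is at stake is the cognitive part of the hypothesis that more blood can be collected without harm to donors' health or well-being. The article says the trial must be able to detect even subtle changes, and a small effect is the kind that this adjustment could blur.

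**Working it through.** **1. The two sections side by side.**

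| Question | Data collection at the 2-year assessment | Data analysis |
|---|---|---|
| Is mood used for adjustment? | Yes, as the stated purpose of the items | Not mentioned |
| When are covariates measured? | At 2 years, just before the tests | At baseline |
| Main or supportive result? | Not said | Baseline value of the outcome in the main analysis where there is one; other baseline characteristics in secondary analyses |

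No cognitive test is listed at baseline, so the Principles section read alone leads to a main comparison of cognition without a baseline cognitive covariate, and a secondary one adjusted for baseline characteristics. A 2-year mood adjustment has no place in either.

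**2. Size.** The article gives no figure for cognition or mood, so there is none to reproduce. What follows is an illustration.

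Inputs from the article: 50,000 participants; three arms in each sex, 1:1:1; up to one third not completing the final questionnaire; type I error 0.05. Assumptions: an equal split by sex, a two-sided test, cognition and mood in SD units, and a total effect of -0.05 SD.

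- Completers per arm: 50,000/6 × 2/3 ≈ 5,556.
- Standard error of an unadjusted difference: √(2/5,556) ≈ 0.019 SD.
- Let *a* be the effect of the shorter interval on mood and *b* the slope of cognition on mood within arm. Then adjusted effect = total effect − *a*·*b*, and share removed = *a*·*b* / total effect.
- Worked case, *a* = -0.10 and *b* = 0.2: adjusted = -0.05 − (-0.10 × 0.2) = -0.03 SD; share removed = -0.02/-0.05 = 40%.
- Power without mood in the model: 75%. With mood, the residual SD is taken as √(1 − *b*²).

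| Effect on mood, *a* (SD) | Share removed, *b* = 0.1 / 0.2 / 0.3 | Power after mood adjustment, *b* = 0.1 / 0.2 / 0.3 |
|---|---|---|
| 0 | 0% / 0% / 0% | 75.4% / 76.7% / 78.9% |
| -0.02 | 4% / 8% / 12% | 72.0% / 69.7% / 68.1% |
| -0.05 | 10% / 20% / 30% | 66.4% / 57.6% / 49.0% |
| -0.10 | 20% / 40% / 60% | 56.3% / 36.5% / 19.6% |

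**3. Check by simulation** (2,000,000 records, total effect set at -0.05 SD).

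| Setting | Unadjusted | Mood-adjusted |
|---|---|---|
| *a* = -0.10, *b* = 0.2, no common cause | -0.0502 | -0.0308 |
| Same, with an unmeasured common cause of mood and cognition | -0.0499 | -0.0142 |
| *a* = -0.10, mood has no causal effect, common cause present | -0.0481 | -0.0322 |
| *a* = 0, *b* = 0.2, no common cause | -0.0496 | -0.0493 |
| *a* = 0, *b* = 0.2, common cause present | -0.0512 | -0.0504 |

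The third row shows that the estimate can move even when mood does nothing to cognition. The last two show that essentially nothing is lost when the interval leaves mood unchanged.

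**4. Direction.** The sign is not fixed. If mood were better in the shorter-interval arm, say *a* = +0.10 with *b* = 0.2, the adjusted effect would be -0.05 − 0.02 = -0.07 SD, which overstates the harm.

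**The case against.** The sentence about mood is half a line explaining why an instrument is included. It names no model, no contrast and no status for the adjusted result. The section that governs the analysis names baseline covariates only and, taken by itself, already gives the comparison asked for here. The covariate set for one of several other secondary outcomes is commonly left to the statistical analysis plan, which is not shown. The five items are not shown either. If they record only how the person feels on the test day, the interval is less likely to affect them, and adjusting would slightly improve precision, as the first row of the power table shows.

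Most of this stands, and it limits the claim. A reader might infer that the protocol commits its main cognitive analysis to mood adjustment. It does not: main or supportive status is not given. A reader might also infer that the bias must run toward no harm, or that a third to a half of an effect would be lost. Both need assumed values for the effect on mood and the slope, and the article supplies neither.

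What does not stand is that the matter is only missing detail. The article states adjustment as the purpose of a variable measured after randomisation, and that purpose does not fit its own analysis section. Whether the items are harmless depends on an effect of the interval on mood that is not known in advance, which is a reason to keep them out of the main comparison.

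**Conclusion.** The point holds as an inconsistency with a possible consequence. One section gives adjustment of the cognitive results as the purpose of a 2-year mood score; the analysis section promises intention-to-treat comparisons with baseline covariates. Because the allocated interval could plausibly affect mood, the adjustment could remove part of an effect on cognition or add bias from shared causes, in either direction.

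For an assumed total effect of -0.05 SD, the loss from a worsening of mood runs from 0% to 60% over the range shown. Every value of the total effect, the mood effect and the slope is an assumption, as is the equal sex split, so the range shows sensitivity and does not predict the bias. The primary outcome and the physical component score are not affected.

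**What to change.** Reconcile the 2-year assessment section with the Data analysis section by stating three things:

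1. The main randomised comparison of cognitive function is not adjusted for mood at 2 years.
2. Covariates are limited to baseline measures, as the Principles section already has it. The baseline SF-36v2 mental component score stays in the secondary adjusted analysis where it is already planned; moving it into the main model would be a preference and is not needed.
3. Any result adjusted for 2-year mood is labelled as a supportive or mediation analysis.

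The cost is wording only. No new data are needed, and the mood items can still be collected.
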